### Sample Size

As this is a proof of concept study, we have provided an exemplar power calculation to assess how the social network clustering of smoking-related social norms might change after a prevention intervention (${\text{H}}_{0}^{5}$). This draws on the work of Krupka who studied ~200 Michigan university freshmen before and after a single semester. Krupka did not have data on smoking *per se* among the freshmen, but did have their elicited time and risk preferences. These measures of preferences are more fundamental behavioral economic traits that are correlated with smoking behaviors (46). Using the basic Clauset et al. community detection algorithm (47), with a sample size of ~200, and with data from two waves, Krupka found that a one standard deviation (*SD*) increase in risk preferences of an individual's friends or social network is associated with an increase of 1/8 to 1/10th of a SD (of the same variable) for the individual. Assuming that clustering of risk preferences is a reasonable proxy for clustering of social norms related to smoking that we will elicit, we estimate that a sample size of 300 would give over 80% power to detect, as statistically significant at the 5% level, a slope of 0.16. In other words, an increase of 0.16 *SD*s in individual norms sensitivity, per *SD* increase in norms sensitivity of those in the individual's social network.

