### Statistical Methods

#### Elicitation of Social Norms and Social Network Analyses

Injunctive social norms will be modeled quantitatively, such that a decision maker's “pay-off” u(a_k_) from a set of actions V {π(a_k_)} is related to the parameter γ ≥ 0, representing the degree to which the individual cares about adhering to social norms, in: u(a_k_) = V {π(a_k_)} + γN(a_k_), with the function N capturing the social norm, [i.e., the social appropriateness of action a_k_ denoted by N(a_k_)]. We let N_g_(a_k_) denote the social norms for group *g*, estimated from the Coordination games. γ is the key parameter reflecting individual sensitivity to the norm, estimated using the total number of balls allocated to the blue “rule following” bucket in the RF task. The Dictator and Coordination games allow us to identify norms related to prosocial behavior and to smoking related activities in the target population. We can then explore whether the norms related to smoking actually do change and whether data from the RF experiments help us predict who is more sensitive to following those changed norms after the intervention. We will also measure correlations (Spearman's rank correlation) between an individual's norms-sensitivity parameter and his/her decisions in the Donation game. We will use tobit regressions that allow for censoring, regressing the distance (Δ_SNdist_) between an individual's choice and the observed average norm (average Dictator choice) in the relevant reference group on his/her norm-sensitivity parameter. The tobit regression allows us to see if there is a statistically significant relationship between norm-sensitivity and the changed norms after the intervention. We will use similar techniques when examining social norms related to tobacco use and individuals' abilities to identify them in the Coordination game. For each behavioral vignette (whose appropriateness is rated), we will calculate a correlation between individuals' norms-sensitivity parameters, and their chosen score on the social appropriateness scale, after calculating (Δ_SNdist_). Scores on the appropriateness scale are categorical, requiring ordered probit regressions. We will conduct the above analysis both pre- and post-intervention but since we will have two observations for each individual, we will use the respective panel random effects versions (including a dummy variable to identify post-intervention observations). In all regressions, we will calculate standard errors clustered on school classes. We will account for individual participants' demographic and psychosocial characteristics, and dummy variables signifying intervention type (ASSIST or Dead Cool intervention) and country (Colombia or Northern Ireland).

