${\text{H}}_{0}^{3}$**: that social norms at the class and year group level are independent of social network structure**: a novel aspect of this proposal is that we will examine how social norms sensitivities (Δ_SNdist_) cluster among friendship groups (before and after the two interventions), and thus examine possible mediating mechanisms for the intervention effects and whether they are moderated by social network structure. We will extend the clustering method presented by Grimmer and King (70), using a Markov Chain Monte Carlo (MCMC) model to integrate various attributes of the students and their social norms sensitivity parameters in the first step of the *a posteriori* clustering selection framework. Examining the influence of individual student attributes (their norms sensitivities; psychosocial traits like self-efficacy, and the number of family members who smoke) within a MCMC framework permits inference based on well-known expectation and maximization algorithms. We note that peer influence was inferred using hidden Markov models (7) applied to *before* and *after* data from three ASSIST schools, but with a similar per country sample size as Steglich et al. (7), we will obtain superior experimental measures of norms and thus populate the MCMC models with real rather than inferred parameters. If homophily is not stable over one semester, in a sensitivity analysis we will use an instrumental variable approach, instrumenting on orthogonal characteristics of students not nominated by the ego but who were friends of their friends, using characteristics that should not plausibly predict the egos' norms sensitivity (Δ_SNdist_), nor friendship structure (71).

${\text{H}}_{0}^{4}$**: that the changes in smoking related norms are the same in schools which were offered the ASSIST intervention and in those which were offered the Dead Cool intervention**: we will use a regression based approach permitting adjustment for the multilevel clustered nature of the data, comparing the change in smoking related norms (identified through the Coordination games) in ASSIST and Dead Cool Schools and between UK and Colombian Schools.

${\text{H}}_{0}^{5}$**: that any changes in social norms are independent among members of the same friendship clique**: see section sample size.

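### H3 uses pupils' norm sensitivity to form the clusters and also examines how norm sensitivity clusters, with no stated safeguard against circularity

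*Protocol article*

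**What the plan says.** All of this is in the protocol article, Statistical Methods, under Elicitation of Social Norms and Social Network Analyses, unless another section is named.

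- The H3 null is "that social norms at the class and year group level are independent of social network structure".
- The quantity to be examined: "we will examine how social norms sensitivities (Δ_SNdist_) cluster among friendship groups (before and after the two interventions"). Possible mediation of the intervention effects, and moderation by network structure, are to be drawn from this step.
- The method: a published clustering approach is extended with an MCMC model "to integrate various attributes of the students and their social norms sensitivity parameters in the first step of the" after-the-fact selection among clusterings.
- The same sensitivities return as a factor under study: "Examining the influence of individual student attributes (their norms sensitivities; psychosocial traits like self-efficacy, and the number of family members who smoke") in the MCMC framework, which the article says "permits inference based on well-known expectation and maximization algorithms".
- Two different quantities carry the sensitivity label. Earlier in the section, "γ is the key parameter reflecting individual sensitivity to the norm, estimated using the total number of balls allocated to the blue" bucket in the Rule-Following task. There, Δ_SNdist is the outcome of a tobit model "regressing the distance (Δ_SNdist_) between an individual's choice and the observed average norm" on that parameter. The H3 text attaches Δ_SNdist to norm sensitivity.
- Sample Size describes a route based on a "community detection algorithm (47), with a sample size of ~200". That example is for H5, and H2 is referred to it. H3 is not.

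**The concern.** If pupils are sorted into clusters partly by their own sensitivity scores, the clusters differ on those scores even when friendships have nothing to do with them. An ordinary test of sensitivity across such clusters partly measures the sorting. Its nominal 5% level applies only to groups formed without looking at the outcome. Choosing among several clusterings afterwards adds a further data-dependent step.

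This matters because the study is about mechanism. A finding that sensitivity clusters among friends is meant to support statements about mediation and moderation through the network. If the groups were built on sensitivity, that finding could not be told apart from an artefact of the grouping.

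**Working it through.** **Is there a figure to reproduce?** Not for H3: no sample size, power, error rate or test statistic is stated. The neighbouring design effect (H1) reproduces: 1 + (100 − 1) × 0.01 = 1.99, so effective N = 600/1.99 = 301.5. It has no bearing on this point.

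**Inputs from the article.** About 100 pupils per school, six schools per country, a 5% level (taken from the H5 power example), and roster-assisted friendship nominations (Social networks and pro-sociality).

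**Assumed, because the article gives none of it.** Network density, number of clusters, a spectral embedding of the ties, k-means clustering, an ANOVA of sensitivity across clusters (within school where schools are pooled), and the weight of sensitivity relative to the network dimensions. Weight 1 means equal scaling. Sensitivity was generated independently of friendships, so every rejection is false.

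**One setting by hand.** Take 100 pupils in 12 clusters per school. With clusters unrelated to sensitivity, the expected between-cluster share of variance is (12 − 1)/(100 − 1) = 11/99 = 0.11. Simulated tie-only clusters gave 0.11. When sensitivity was added to eight network dimensions at equal weight, the share rose to 0.28. Pooling six schools, the degrees of freedom are 6 × 11 = 66 and 6 × 88 = 528:

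- Share 0.11: F = (0.11/66)/(0.89/528) = 0.99.
- Share 0.28: F = (0.28/66)/(0.72/528) = 3.11.
- The 5% critical value of F(66, 528) is 1.33.

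An average F of 3.11 against 1.33 explains why this setting rejected in 100% of 300 simulated countries, against 5.3% for ties only.

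**Across settings.** Rejection rates at nominal 5%, giving the range over all network settings tried:

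| Clustering input | One school of 100 | Six schools pooled |
|---|---|---|
| Ties only, or ties plus unrelated traits | 3–8% | 2–6% |
| Sensitivity added, weight 0.25 | 6% | 11–20% |
| Sensitivity added, weight 0.5 | 4–7% | 8–84% |
| Sensitivity added, weight 1 | 16–79% | 44–100% |
| Sensitivity added, weight 1.5 | 85–99% | 100% |
| Sensitivity added, weight 2–3 | 99.8–100% | not run |
| Traits and sensitivity, no ties | 96–100% | not run |

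Runs per setting, where recorded, were 100 to 400. At 400 runs, the standard error around a true 5% is √(0.05 × 0.95/400) = 1.1 points; at 100 runs it is 2.2 points. The tie-only row is therefore consistent with the nominal level.

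Three patterns follow. Groups formed without sensitivity hold the level. Inflation grows with the weight on sensitivity, and is larger with a weaker network. Pooling schools accumulates it, and pooled data are closer to the planned analysis, with about 600 pupils per country.

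**If the input and the examined measure differ.** With one measure as clustering input and a different one examined, one-school runs at correlations of 0 to 0.6, mostly at equal weight, gave about 3–8%. With six schools pooled and a correlation of 0.3, the rate was about 21–22%. Separating γ from Δ_SNdist reduces the problem but does not reliably remove it.

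**The case against.** The strongest reply is that the circular test is not written down. The article does not say that the clusters formed with sensitivity are the friendship groups examined. Friendship nominations are collected separately, and groups taken from them alone would hold the level. This stands: circularity is not excluded, rather than stated. It does not dispose of the point, because H3 is given its own method, that method has sensitivity as an explicit input, and it is not referred to the community detection example as H2 is.

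Secondly, a joint model of grouping and attributes is not circular merely because an attribute enters it. That is correct in principle, and the detail of the extended method may sit in a fuller document. But the article names sensitivity as an input to the first step and, for H3, states no reference distribution that allows for it.

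Thirdly, the formal null concerns norms at class and year-group level, while the simulations test pupils' sensitivities. This also stands. The rates above describe the clustering examination that the article sets out under H3, not a test of the null as literally worded.

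A reader might go further and infer that H3 is rejected almost by construction, that it would be supported whatever the truth, or that the before-and-after comparison cannot show change. The documents do not support these. Weight and test statistic are unspecified, rates at low weight can stay near nominal, and the claim about change was not examined. Nor does the formal mediation model inherit the problem: under Mediation Analyses it is a cross-lagged panel model on psychosocial traits and does not use these clusters.

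**Conclusion.** The point holds in conditional form. As written, the H3 method feeds norm sensitivity into cluster formation and examines the clustering of norm sensitivity, with no safeguard. If the formed clusters are the groups examined, the false-positive rate exceeds 5%. With six schools pooled, the simulations gave 8% or more at every weight tried and 44–100% at equal weight, against 2–6% for tie-only groups.

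These magnitudes rest on assumed network density, embedding, clustering algorithm, weights and test. They show direction and possible size, not the error rate of the actual analysis. They also depend on γ and Δ_SNdist being the same or correlated measures, which the article leaves unclear. The flaw lies in a stated method and not only in missing detail, so it should be settled before any inference is drawn from H3.

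**What to change.** For H3 inference:

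1. Form friendship groups from the nomination ties only, for example with the community detection algorithm already cited in Sample Size. Keep γ, Δ_SNdist and the elicited norms out of the clustering step.
2. Test the association of norms or sensitivity with those groups against a within-school permutation of pupils' values over the fixed network.
3. State which measure, γ or Δ_SNdist, is examined as norm sensitivity.

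If the attribute-informed clustering is to be kept for inference, use a permutation reference that repeats the whole clustering and selection step on each permuted data set. Otherwise, label it descriptive.

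The cost is a change of wording and a simpler clustering input; no new data are needed. Repeating the clustering within each permutation adds computing time. The one loss is that the attribute-informed clustering, which the article presents as novel, would no longer support inference on its own.

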Two competing theories have been offered about how health-related attitudes and behavior evolve and are transmitted across social networks, namely: (i) *selection* (homophily)—the tendency for people to establish relations with those they perceive to be most like (similar to) themselves; and (ii) by *influence*, whereby one adopts the behaviors that are seen as normative within the peer environment. Most observational studies show that both processes operate to varying degrees. Valente and Pitts (14) have recently articulated social networks' influence on behavior in terms of “the pressure individuals feel to conform to behavior when others in equivalent positions do so” and offers two putative mechanisms: (i) one via threshold effects whereby, for example, “low threshold” individuals adopt a new behavior before many of their peers have done so; (ii) and a second that weights “exposure” (and influence) according to structural characteristics of the network. While social networks are increasingly being exploited in the design and implementation of public health interventions (8, 15), a growing number of studies are now also testing interventions based on changing social norms related to health behaviors (16).

Within public health science, there have been few empirical studies exploring the *mechanisms* underlying the influence of social norms on health related attitudes and behavior. *Game Theory* is a branch of economics that has developed a canon of well-defined mathematical models for describing and understanding cooperation and competition amongst individuals and groups. However, while Game Theorists have increasingly adopted experimental approaches to test their more sophisticated models of social norms effects (17), the resulting insights have not crossed the disciplinary divide into the public health sciences. Previous attempts at identifying individual sensitivity to the effects of social norms have relied on actor-based *models* and have not actually attempted to empirically measure the effects directly. An experimental design rooted in Game Theory offers new ways to do this, and provides the opportunity to explore the behavioral economic mechanisms underlying the influence of social norms on health related attitudes and behavior.

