### The Role of Game Theory Experiments in Studying Social Norms and Peer Influence

Kimbrough et al. (18) show that one can use simple rule following games to identify individual sensitivity to social norms. This norm sensitivity is a good explanation for cooperation, reciprocity and prosocial behavior in *Trust, Public Goods, Dictator*, and *Ultimatum* Games. Krupka et al. (20) use norm elicitation experiments to show that informal agreements affect behavior through a direct effect on the social norm and through an indirect effect by which the social norm appears to influence beliefs. These findings are significant because they identify a channel for behavior change that operates through a change in norms and beliefs at the individual level. This channel is a social channel: the norm is contingent on the peers who establish, transmit, and enforce the norm. However, previous work has not yet tested this channel where it can be most effective—nested within the social network of the individual. This study will test this channel within a social network. We will identify the impact of an intervention designed to change norms and beliefs. We will focus on smoking prevention in adolescents because it is an important public health concern and a critical population to reach.

The key objectives of this study are to:

develop and test new measures of social norms around smoking behaviors in adolescents using Game Theory approaches;better understand the diffusion of social norms in school settings in the UK, and in Colombia;better characterize the potential mechanisms of action of smoking prevention interventions in schools;learn lessons for the design and evaluation of behavior change interventions that invoke mechanisms that change social norms.

Our main research questions include:

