How are individual psychosocial and cognitive traits at baseline related to individual sensitivity to social norms? (**H**_**0**_^**1**^: that they are independent);How does individual sensitivity to social norms cluster among friendship cliques and across school year groups? (**H**_**0**_^**2**^: that the individual social norms sensitivities among friendship cliques are un-correlated);How are average social norms, measured at the classroom and year group level, affected by social network structures? (**H**_**0**_^**3**^: that social norms and social network structures are independent);After each intervention: how are changes in attitudes, intentions and behaviors toward smoking related to social norms sensitivity at the individual level, and to average social norms at the class and year group level? (**H**_**0**_^**4**^: that the changes in smoking related attitudes, intentions, and behaviors are independent of norm-sensitivity at the individual level and the same in schools which offered each intervention);After each intervention: have smoking-related social norms changed and how are these changes correlated among friendship cliques? (**H**_**0**_^**5**^: that any changes in social norms are independent among members of the same friendship clique; we assume that there will be little change in measures of homophily across one semester).

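### The only analysis of friend selection runs if homophily is unstable, but stable homophily does not rule selection out, so it cannot support reading a rejection of H5 as diffusion

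*Protocol article*

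**What the plan says.** In the list of research questions (The Role of Game Theory Experiments in Studying Social Norms and Peer Influence), the null for H5 is "that any changes in social norms are independent among members of the same friendship clique". The same item attaches an assumption: "we assume that there will be little change in measures of homophily across one semester".

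The H5 entry in Elicitation of Social Norms and Social Network Analyses restates the null and refers to Sample Size. There the analysis is illustrated by a slope of 0.16 SD in the individual per SD in that individual's network, with the statement that a "sample size of 300 would give over 80% power to detect" this slope at the 5% level.

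The one step aimed at friend selection stands in the H3 paragraph of the same statistical section: "If homophily is not stable over one semester, in a sensitivity analysis we will use an instrumental variable approach", and specifically "instrumenting on orthogonal characteristics of students not nominated by the ego but who were friends of their friends".

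Two other statements bear on it. On selection and influence, Social Networks and Social Norms says: "Most observational studies show that both processes operate to varying degrees". And the study's purpose includes a peer channel of norm change: "This study will test this channel within a social network". Friendship nominations are collected at baseline and again one week after the intervention ends (Social networks and pro-sociality).

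**The concern.** The condition makes stability of homophily the test of whether selection needs attention. It can mislead in two directions.

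- **Stable homophily with selection at work.** If pupils replace some friends each semester and choose the new ones for similarity, homophily can stay where it is. Changes still correlate. Ties formed by follow-up are chosen on follow-up values, and friends chosen for similar baseline values regress towards the mean together. The condition then leaves the selection analysis switched off.
- **Unstable homophily because influence worked.** Pupils who move towards their friends become more alike. Measured homophily can then rise with no change in ties, and the condition flags a real effect as a selection problem.

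What is at stake is the meaning of H5, the hypothesis chosen for the exemplar power calculation. Correlated change among friends is natural evidence for diffusion through the network, and stable homophily would be offered as the reason for not suspecting selection.

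**Working it through.** **Step 1. The plan's own figure.** Inputs from Sample Size: n = 300, standardised slope 0.16, 5% level (taken as two-sided).

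- Fisher z: arctanh(0.16) × √297 − 1.960 = 0.1614 × 17.23 − 1.960 = 0.821, power 79.4%.
- Wald: 0.16 / √((1 − 0.0256)/300) − 1.960 = 0.848, power 80.2%.

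The stated power of over 80% is reproduced to within rounding. A slope of 0.16 is the yardstick below.

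**Step 2. Set-up.** The article gives no homophily, tie-turnover or autocorrelation figure, so these are assumptions. All simulations use 3 schools × 100 pupils and 5 friends each. Unless noted there is no influence. Homophily is the correlation of the norm over friend pairs at each wave. The test is a pupil's change regressed on friends' mean change at 5%. With neither selection nor influence, this simple test rejected in 7% to 11% of runs, so that is the reference rate rather than exactly 5%.

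**Step 3. All ties re-chosen on the current norm at each wave (600 runs).** Baseline norm variance is 1 and change variance 0.25, so follow-up variance is 1.25.

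- Homophily 0.43 then 0.43: slope 0.17, rejected in 79%.
- Homophily 0.66 then 0.67: slope 0.25, rejected in 97%.

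A hand check of the first case: regressing change on the follow-up norm gives 0.25/1.25 = 0.20. The pair correlation of changes is therefore 0.20² × 0.427 × 1.25/0.25 = 0.085. Dividing by √(1/5) = 0.447 for the mean of five friends gives 0.19. Adding the offset of −0.02 seen with no selection gives 0.17, as simulated.

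**Step 4. Partial turnover: 2 of 5 ties replaced, autocorrelation 0.5.** Two separate implementations of re-choice by similarity, homophily stable in each:

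| Implementation | Homophily | Follow-up ties | Baseline ties | Baseline ties, own and friends' baseline norm adjusted |
|---|---|---|---|---|
| A (250 runs) | 0.10 | 10% | 6% | 5–6% |
| A | 0.21 | 23% | 16% | 5–6% |
| A | 0.39 then 0.38 | 62% | 35% | 5–6% |
| B (150 runs) | no selection | 11% | 10% | 7% |
| B | 0.11 | 25% | 12% | 5% |
| B | 0.21 | 69% | 36% | 5% |
| B | 0.33 | 99% | 73% | 5% |

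A further simulation of friend re-selection, with homophily unchanged at 0.13 to 0.35, gave 38–100% on follow-up ties and 19–84% on baseline ties. At the same homophily of 0.21, A and B give 23% and 69%: the direction is consistent, the size is not.

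**Step 5. Fixed ties, friends alike on a second trait that drives change (600 runs).** Homophily was stable at 0.09, 0.17 and 0.28. Slopes were 0.21, 0.36 and 0.51, with rejection in 93%, 100% and 100%. Baseline ties do not help here, because no tie changes.

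**Step 6. Fixed ties, friends chosen on a stable latent trait that the norm score measures with noise (500 runs).** Homophily 0.13, 0.22 and 0.31: raw change-on-change rejected in 7%, 7% and 8%, but the baseline-adjusted model in 29%, 66% and 86%. The ranking of Step 4 is reversed.

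**Step 7. Influence with fixed ties.** Influence towards friends' baseline level, weight 0.15 or 0.30, raised homophily in all six settings: −0.01 to 0.02 or 0.06; 0.21 to 0.22 or 0.25; 0.32 to 0.34 or 0.39. In these settings the raw change slope was negative (−0.05 to −0.22), so its sign does not track influence either. When only new shocks spread among friends already alike in level, homophily fell from 0.21 to 0.17.

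**The case against.** The strongest defence is that H5 is stated as independence of changes within cliques. If selection makes friends' changes correlate, that null is false and rejecting it is correct. This stands. A reader might take the rates above as an inflated type I error for H5; they are not. They show how often a true association without influence would be found.

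A reader might also infer that the article declares selection ignorable. It does not, and its background section says that both processes operate. The conditional sentence is printed under H3 and concerns norms sensitivity. But the homophily assumption is attached to H5 by name, and no other step addresses selection.

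It can be said, too, that the wave defining friends and the baseline adjustment belong to a fuller plan, and that Sample Size gives only an exemplar slope, in norms sensitivity. That is fair: their absence is not counted as an error, and the change-on-change regression is a reading of H5. The stability condition, however, is stated in the article itself.

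On size, if the cited slope of 1/10 to 1/8 SD is a rough guide to homophily, the effect on baseline ties is close to nothing (6% and 12%, against a reference rate of 7% to 11%). And if influence trips the condition, the cost is one added sensitivity analysis.

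**Conclusion.** The concern holds as a fault in the stability condition and in the inference it would support. Stable homophily does not show that selection is absent. With no influence and homophily unchanged, selection produced friend-change slopes at or above the planned detectable 0.16 in Steps 3 and 5, and rejection well above the reference rate in most re-selection settings. The size runs from negligible at homophily near 0.10 on baseline ties to near-certain rejection, and depends on values the article does not supply.

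Two stronger readings are not supported. Influence does not always raise homophily: Step 7 has a counter-example. And adjusting for own and friends' baseline norm is not a cure: it works when friends are chosen on the score itself (Step 4) and misleads when they are chosen on a stable trait behind it (Step 6).

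H5 may be tested as planned. Its rejection should not be reported as diffusion or peer influence on the strength of stable homophily.

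**What to change.** 1. Remove the stability condition and run the instrumental-variable sensitivity analysis in every case.
2. Define friends for the main H5 analysis by baseline nominations.
3. Always report tie turnover between waves and an analysis restricted to ties present at both.
4. Show the friend-change slope with and without adjustment for own and friends' baseline norm, as sensitivity analyses, stating that neither form is robust to every selection mechanism.
5. Report H5 as an association unless these analyses agree.

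The cost is plan wording and a little more analysis; nominations and norms are already collected at both waves. The downside is some dilution of an influence effect where baseline ties dissolve.

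### H0-4 is stated as two different nulls, and no described analysis links change in smoking attitudes, intentions or behavior to norm sensitivity or to group norms

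*Protocol article*

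**What the plan says.** The research questions stand at the end of the protocol article's section on the role of game theory experiments. Question 4 asks "how are changes in attitudes, intentions and behaviors toward smoking related to social norms sensitivity at the individual level", and also how those changes relate to average norms in the class and year group. Its null has two parts: "that the changes in smoking related attitudes, intentions, and behaviors are independent of norm-sensitivity at the individual level and the same in schools" under either intervention.

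The statistical methods (Elicitation of Social Norms and Social Network Analyses) restate H0-4 as "that the changes in smoking related norms are the same in schools which were offered the ASSIST intervention" and in those offered Dead Cool. The analysis is a regression allowing for clustering, "comparing the change in smoking related norms (identified through the Coordination games) in ASSIST and Dead Cool Schools and between UK and Colombian Schools". Mediation Analyses also cites H0-4 as the relation between intervention and smoking-related norms.

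The same methods section describes tobit models "regressing the distance (Δ_SNdist_) between an individual's choice and the observed average norm (average Dictator choice) in the relevant reference group" on the individual's norm-sensitivity parameter, and ordered probit models for the appropriateness ratings. Both become random-effects panel models, "including a dummy variable to identify post-intervention observations", with adjustment for pupil characteristics, intervention and country. The article says that the tobit will show whether norm sensitivity is related to the norms as changed after the intervention.

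**The concern.** One label carries two nulls with different outcomes. If the methods text is followed, H0-4 can be accepted or rejected on norms alone while the question put to the reader, whether pupils who are more sensitive to norms change their smoking attitudes, intentions or behavior differently, is never estimated. Two texts also leave room to choose the version after the data are seen.

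The panel models raise a narrower issue. They are offered as evidence on norm sensitivity and changed norms, but the terms listed would give a sensitivity coefficient that pools both waves.

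**Working it through.** **1. The two H0-4 texts side by side.**
- Research questions: outcomes are changes in attitudes, intentions and behaviors. Part (a) is independence from individual norm sensitivity; part (b) is equality between interventions. The question itself adds class and year-group average norms.
- Statistical methods: the outcome is change in smoking-related norms. Only equality between interventions remains. Mediation Analyses follows this version.
- The nulls for H0-1, H0-2, H0-3 and H0-5 are essentially the same in both places. Only H0-4 changes content.

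**2. Does any described quantitative analysis cover the research-question version?**
- H0-1 regression: psychosocial traits against norm sensitivity. The question concerns baseline traits, not change.
- Tobit and ordered probit panels: outcomes are distance from the average norm and appropriateness ratings.
- Spearman correlation: norm sensitivity against donation decisions.
- H0-2, H0-3 and H0-5: clustering of norm sensitivities or of changes in norms among friends.
- H0-4 regression: change in norms by intervention and by country.
- Mediation models: intervention predicts each mediator at time 2, with the time 1 mediator in the model. The section on hypothesized mediators lists both attitudes and intentions, so part (b) has a baseline-adjusted estimate for those two. The models are then repeated for smoking behavior/intentions; no direct path from intervention to the time 2 outcome is listed, so coverage of behavior is partial. Norm sensitivity and class or year-group average norms are not among the listed predictors.

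Result: part (b) is partly covered. Part (a), and the class and year-group norm question, have no described analysis.

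**3. What the sensitivity coefficient measures in the panel models.** The document gives no figure to reproduce, so this is an illustration. Take the linear analogue with equal numbers at both waves, and with sensitivity g held at one value per pupil. Let the slope on g be b0 before and b1 after.
- Main effects only (post, g): coefficient on g = (b0 + b1)/2.
- With post × g added: coefficient on post × g = b1 − b0, the change.

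Assumed slopes b0 = +0.15 and b1 = −0.15:
- main effects: (0.15 − 0.15)/2 = 0;
- interaction: −0.15 − 0.15 = −0.30.

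A least-squares simulation (assumed: 600 pupils, two waves, equal arms, outcome SD about 1, 300 replicates) averaged 0.001 for the main-effects coefficient and −0.296 for post × g. In the special case b0 = 0, the pooled coefficient is b1/2.

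**The case against.** The strongest reply is that this is a condensed article on a proof-of-concept study, and that product terms are usually left to a fuller plan. That stands in part. No regression equation is printed and interactions are not ruled out, so the fair statement is that none is named. The section on willingness to pay even predicts a larger effect among more rule-following pupils, so the idea of moderation is present. But the article does claim an inference about changed norms from the tobit, and the listed terms do not deliver it. Condensing also does not explain two different nulls under one number.

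A second reply is that questionnaire measures of injunctive and descriptive norms are among the hypothesized mediators, so the repeated mediation models do link norms to behavior and intentions. They do, but through each pupil's own reported perceptions. These are neither norm sensitivity nor a class or year-group average.

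Three stronger readings are tempting and are not supported:
- **That none of the three H0-4 outcomes is tested, or that question 4 is wholly unanswered.** The mediation models estimate an adjusted intervention effect on attitudes and intentions.
- **That the intervention comparison fails because the panel models carry only an intervention dummy.** That dummy and the country dummy are presented as adjustment terms. The separate H0-4 regression compares change in norms by intervention and by country directly.
- **That the pooled sensitivity coefficient will be exactly half the true effect.** That needs a linear model, balanced waves and a zero slope before the intervention. The planned models are tobit and ordered probit, where exact averaging need not hold.

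**Conclusion.** The concern holds in this limited form and should be fixed. The H0-4 texts are incompatible: the outcome differs and the norm-sensitivity part is missing from the methods. As described, no analysis relates change in attitudes, intentions or behavior to individual norm sensitivity or to class or year-group average norms. This rests on reading the text and on no numerical assumption.

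The panel-model point is secondary. With main effects alone, the sensitivity coefficient mixes the before and after slopes and does not measure change. The simple-average result assumes a linear, balanced model with one sensitivity value per pupil. The effect sizes in the illustration are assumed, so they show the mechanism and do not predict the bias in this study.

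The article lists five main questions without ranking them and uses H0-5 for its exemplar power calculation. The gap therefore affects one of five questions and leaves the others as they are.

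**What to change.** 1. Reconcile H0-4 across the research questions, the statistical methods and Mediation Analyses. One way is to keep the research-question null as H0-4 and to give the comparison of norms between interventions its own label. The documents do not settle which version was intended, so the investigators should decide and record it before analysis.
2. Add a regression, with clustering allowed for, of each follow-up attitude, intention and behavior on its baseline value, baseline norm sensitivity, class or year-group average norm, and intervention.
3. Name a post × norm-sensitivity term in the panel tobit and ordered probit models, and base any statement about changed norms on that term.

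The cost is wording and a few extra regressions on data the plan already collects at both time points. The main limitation is precision for the group-level norm term: there are six schools in each country, 6 + 6 = 12 in all, so that coefficient should be reported with its interval and read cautiously.
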